### Blinding method

This will be a double-blind study. In the post-operative period, patients will receive either the antibiotic therapy (ceftriaxone-metronidazole or levofloxacin-metronidazole) or the placebo. Both will be injected intravenously for 3 days. The placebo will be formulated in the same format as the antibiotics. The investigators evaluating the primary endpoint will be blinded to the treatment group, as well as the included patients. The nurses who perform the injection will not be blinded. The vigilance unit must have a copy of the randomization list or a set of envelopes for unblinding.

Unblinding will be performed by the vigilance unit if the occurrence of an unexpected serious adverse effect (SAE) is suspected before declaration to the competent health authorities and annually when annual safety reports are drafted*.*

### Participating centers

The patients will be recruited with help from the *Federation de Recherche EN CHirurgie* (FRENCH) centers that have already participated in another randomized control trial funded by the PHRC (the ABCAL trial, in 2009) [27].

### Statistical methods

#### Sample size

The patients will be randomized into two groups, 1 and 2. Group 1 will not receive post-operative antibiotic therapy (the experimental group) and group 2 will receive post-operative antibiotic therapy (the control group). The groups will be compared in terms of the primary endpoint (i.e., the incidence of organ/space SSIs). The study is based on a non-inferiority analysis.

The hypothesis of the study is that the absence of post-operative antibiotic therapy is at least as good as or similar to the presence of post-operative antibiotic therapy. Furthermore, we assume that the incidence of organ/space SSIs in the reference group is 12%.

The expected organ space SSI rate of 12% in the population of patients with CAA who undergo laparoscopy is based on the publication by Van Rossem et al. [17]. With a non-inferiority margin of 5%, a two-sided alpha risk of 5%, a beta risk of 20%, and a loss-to-follow-up rate of 10%, the calculated sample size is 1476 included patients, i.e., 738 per group. Due to three interim analyses at 10%, 25%, and 50% of the planned sample size, the total sample size increases to 1494 patients (747 per arm). The sample was calculated using the equation on page 290 of the book by S Piantadosi (*Clinical trials: A Methodological Perspective* (2nd edition), John Wiley and Sons, Hoboken, 2005).

#### Statistical methods

Qualitative variables will be presented as numbers (percentages) and compared using a chi-squared test with Yates’ correction or (if applicable) Fisher’s test. Quantitative variables will be presented as the means ± standard deviation or medians (interquartile range) and compared using Student’s *t*-test or a Wilcoxon signed-rank test, as appropriate. Kaplan-Meier curves for the time to event will be built and compared using a log-rank test.

A detailed statistical analysis plan will be defined and validated by the study’s scientific advisory board. Any modifications must be made before unblinding of the database and must be validated by the scientific advisory board.

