##### Analysis of the primary endpoint

Non-inferiority will be established if the upper limit of the two-sided 95% confidence interval of the difference in the proportion of infections between the two groups (placebo arm – antibiotic arm) is lower than the non-inferiority margin (5%). An intention-to-treat analysis will be followed by a per-protocol analysis. A multiple imputation analysis will be performed if more than 5% of the data are missing for the primary endpoint.

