##### Analysis of secondary endpoints

The patient-related endpoint, consisting of quality of life prior to surgery, on discharge, and on POD 30 after surgery, will be assessed in a mixed model analysis of variance with a Bonferonni-Holm closed testing procedure for post hoc analyses.

In terms of the infection-related endpoints, the proportion of patients with superficial SSIs will be assessed using a chi-squared test or Fisher’s test. The post-operative infection rates by POD 30, including SSIs and remote infections, will also be assessed using a chi-squared test or Fisher’s test. The number of antibiotic-free days between randomization and POD 30 will be assessed using Student’s *t*-test or a Wilcoxon test. The microbial flora will be assessed using a chi-squared test or Fisher’s test. The proportion of patients with adequate antibiotic treatment will also be assessed using a chi-squared test or Fisher’s test.

In terms of the surgery-related endpoints, morbidity and mortality (according to the Dindo-Clavien classification) will be assessed using a Wilcoxon test, LOS will be assessed using a chi-squared test or Fisher’s test, and the rehospitalization rate will be assessed using a chi-squared test or Fisher’s test.

Statistical analysis will be performed using SAS® software (version 9.4, SAS Institute Inc., Cary, NC, USA).

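### The Yates correction, set as the general rule for binary comparisons, is unnecessary at about 700 patients per arm and makes the secondary tests mildly conservative

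*Protocol article*

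**What the plan says.** Three parts of the protocol article bear on this.

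- **Statistical methods (general paragraph).** The rule is "Qualitative variables will be presented as numbers (percentages) and compared using a chi-squared test with Yates’ correction", or Fisher's test where applicable. This is the only sentence that says which form of the chi-squared test is meant.
- **Analysis of secondary endpoints.** Tests are named endpoint by endpoint, without the correction: "the proportion of patients with superficial SSIs will be assessed using a chi-squared test or Fisher’s test", and "The post-operative infection rates by POD 30, including SSIs and remote infections, will also be assessed using a chi-squared test or Fisher’s test". Microbial flora, adequacy of antibiotic treatment and rehospitalization get the same pair of tests.
- **Analysis of the primary endpoint.** The decision rests on an interval: "Non-inferiority will be established if the upper limit of the two-sided 95% confidence interval of the difference in the proportion of infections" (placebo minus antibiotic) lies below the 5% margin. No chi-squared test enters.

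The general paragraph also refers to a detailed analysis plan, and allows changes before the database is unblinded if the scientific advisory board validates them.

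**The concern.** Yates' correction pulls the chi-squared statistic towards zero so that its p-value approximates that of Fisher's exact test. With small counts that may be wanted. With roughly 700 patients per arm the uncorrected test is already accurate for all but very rare outcomes, and the protocol has Fisher's test in reserve for those. The correction then lowers both the true type I error and the power.

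Two things are at stake, both secondary. First, superficial SSI (called the principal infection-related outcome under Secondary outcomes), all infections and rehospitalization are places where harm from withholding antibiotics could appear beyond the primary endpoint. A conservative test is somewhat less likely to show it. Second, the two sections can be read differently, so two analysts could report different p-values from the same table.

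**Working it through.** **Inputs from the protocol (Sample size).** Reference organ/space SSI rate 12%; margin 5 percentage points; two-sided alpha 5%; power 80%; loss to follow-up 10%; 738 per group before and 747 per arm after allowance for interim analyses.

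**Step 1: reproduce the plan's own figure.** Without a continuity correction,

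n = (1.96 + 0.8416)² × 2 × 0.12 × 0.88 / 0.05² = 7.849 × 0.2112 / 0.0025 ≈ 663.1, so 664 per arm.

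Then 664 / 0.9 = 737.8, so 738 per arm and 1476 in total. This matches the protocol exactly, so the sample size does not rest on the correction. Evaluable patients at the final size: 747 × 0.9 ≈ 672 per arm.

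**Step 2: what the correction does.** With n patients per arm, N = 2n, x₁ and x₂ events and m = x₁ + x₂:

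- uncorrected: χ² = N (x₁ − x₂)² / [m (N − m)]
- Yates: χ² = N (|x₁ − x₂| − 1)² / [m (N − m)]

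With equal arms the correction removes one event from the observed difference. Significance at 5% requires |x₁ − x₂| > 1.96 × √[m (N − m)/N], plus 1 under Yates. At 672 per arm:

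- 12% rate, m ≈ 161: 1.96 × √(161 × 1183 / 1344) ≈ 23.3 events; Yates 24.3.
- 2% rate, m ≈ 27: 1.96 × √(27 × 1317 / 1344) ≈ 10.1 events; Yates 11.1.

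One event in 23 matters little and one in 10 matters more, which is why the effect grows as the rate falls.

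**Step 3: true size.** Every 2×2 table was enumerated for two independent binomial arms, rejecting when χ² > 3.841. Only 12% is a protocol rate; the others are assumptions shown as a range.

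| Rate in both arms | 747 per arm: uncorrected / Yates | 672 per arm: uncorrected / Yates |
|---|---|---|
| 2% | 5.06% / 3.10% | 5.08% / 2.94% |
| 3% | 5.09% / 3.34% | 5.04% / 3.30% |
| 5% | 4.97% / 3.72% | 5.07% / 3.64% |
| 12% | 5.00% / 4.14% | 4.99% / 4.07% |
| 20% | 5.01% / 4.27% | 5.02% / 4.24% |

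**Step 4: power by the same enumeration** (loss in percentage points in brackets).

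| Rates compared | 747 per arm: uncorrected / Yates | 672 per arm: uncorrected / Yates |
|---|---|---|
| 2% v 4% | 63.20% / 56.36% (6.84) | 58.45% / 51.39% (7.06) |
| 3% v 5% | 51.02% / 45.20% (5.82) | 46.86% / 41.15% (5.71) |
| 5% v 8% | 65.47% / 61.68% (3.79) | 61.18% / 56.39% (4.79) |
| 12% v 17% | 78.62% / 76.39% (2.23) | 74.30% / 71.62% (2.68) |
| 15% v 20% | 72.14% / 69.87% (2.27) | 67.58% / 64.96% (2.62) |

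**Step 5: an illustrative table.** With 10 v 21 events at 672 per arm, m = 31 and N − m = 1313. Uncorrected: 1344 × 121 / (31 × 1313) = 4.00, p = 0.046. Yates: 1344 × 100 / (31 × 1313) = 3.30, p = 0.069.

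**Step 6: Fisher's test.** At 747 per arm its true size is 4.18% at a 12% rate and 3.11% at 2%, about as conservative as Yates. Using it widely would bring the same loss back. Expected counts fall below 5 only when the pooled rate is under 5/672 = 0.74%, so a rule based on expected counts confines it to very rare outcomes.

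**The case against.** The strongest reply has four parts.

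1. **The trial's conclusion does not depend on this.** That stands. The primary rule is a confidence interval, and the sample size reproduces without the correction.
2. **The endpoint section does not mention Yates, and the analysis plan may settle the matter.** That stands in part. Applying the correction to the secondary endpoints is an inference from the general sentence. But that sentence fixes a form of the test, and nothing in the article withdraws it for these endpoints.
3. **The larger losses rest on rates the protocol never gives.** That stands. All infections by POD 30 include the primary outcome, so under the design assumption their rate is at least 12%, where the effect is smallest. No expected rate is given for superficial SSI or rehospitalization.
4. **Yates and Fisher are valid tests, and preferring an uncorrected test is a matter of taste.** Both do hold the error rate below 5%. At this size, however, the uncorrected test holds it too, with more power, and Fisher's test is available for sparse tables. The correction therefore protects against nothing here.

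A reader might also infer that the correction tilts the trial towards its hypothesis that post-operative antibiotics have no value. The documents do not support that. The correction treats the arms alike, the hypothesis is tested by the interval rule, and nothing says that a non-significant secondary test will be taken as proof of no difference. Adequacy of treatment concerns bacterial sensitivity in the perioperative sample, so it is not an excess-harm outcome.

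**Conclusion.** The point holds as a minor one, limited to the binary secondary comparisons. As the general rule is written, the correction is unnecessary and makes those tests mildly conservative. At the protocol's 12% rate, true size is about 4.1% and the power loss for 12% versus 17% is about 2 to 3 points. At assumed rates of 2% to 5%, true size is about 2.9% to 3.7%. The loss is about 4 to 6 points for 3% versus 5% and 5% versus 8%, and about 7 for 2% versus 4%. The secondary endpoints carry no stated power target, so no promised power is broken.

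Two stronger readings should be avoided. One is that the trial's tests in general run far below 5%; that description fits only low rates, which the protocol does not state. The other is that the non-inferiority test is weakened; the protocol does not put a continuity correction into that interval.

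The figures assume independent binomial arms of equal size, 672 to 747 patients each, and a two-sided 5% test.

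**What to change.** In the general paragraph of Statistical methods, replace the Yates-corrected test with the uncorrected Pearson chi-squared test, and reserve Fisher's exact test for tables with an expected count below 5. Use the same wording in Analysis of secondary endpoints so that both sections name one test.

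The cost is a few words in the protocol or analysis plan. It needs no extra patients, visits or data, and fits the protocol's own provision for changes validated by the scientific advisory board before unblinding. The primary analysis and the sample size stay as they are.

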##### Analysis of the primary endpoint

Non-inferiority will be established if the upper limit of the two-sided 95% confidence interval of the difference in the proportion of infections between the two groups (placebo arm – antibiotic arm) is lower than the non-inferiority margin (5%). An intention-to-treat analysis will be followed by a per-protocol analysis. A multiple imputation analysis will be performed if more than 5% of the data are missing for the primary endpoint.

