### Randomization

An interactive web response system will be used to randomize patients using a randomization list with blocks of equal size (with the same number of randomized patients in each group, i.e., antibiotics vs no antibiotics) and stratified by center.

At the end of the surgery, investigators will check the inclusion and non-inclusion criteria. If the patient meets all of the inclusion criteria and none of the non-inclusion criteria, the investigators will log him/her into the electronic case report form and request that a treatment number be allocated to the patient.

The sequence of the study treatments (preoperative and perioperative antibiotic therapy, laparoscopic appendectomy, with or without post-operative antibiotic therapy) will be generated by a data manager using a computer program. The allocation of patients to the different study groups will involve the use of a secure, independent computer to ensure that the investigator cannot interfere with the results of this procedure. Randomization (1:1) will be stratified by center.

Randomization will be performed by an identified investigator. At the end of the surgery, the investigator will log onto the study web site (https://recherche-clinique.chu-amiens.fr/csonline/) using his/her personal username and password. The patient will be registered online and a participant number will be allocated. If the patient satisfies the inclusion/exclusion criteria and stratification criteria, he/she will be randomized, and the investigator will gain access to the treatment number allocated to the patient.

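### Randomization is stratified by center, but the primary difference is worded without a center term and the binary secondary tests are unstratified: valid, but slightly conservative if centers differ (minor).

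*Protocol article*

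**What the plan says.** - **Design.** The Randomization section describes a "randomization list with blocks of equal size" and states the stratification twice, the second time as "Randomization (1:1) will be stratified by center". Center is the only stratification factor named.
- **Primary rule.** Under Analysis of the primary endpoint, non-inferiority is shown if the "upper limit of the two-sided 95% confidence interval of the difference in the proportion of infections between the two groups" (placebo minus antibiotic) lies below 5%. No interval method is named. Center is neither included nor excluded.
- **Binary endpoints.** The general paragraph under Statistical methods has qualitative variables "compared using a chi-squared test with Yates’ correction" or, where applicable, Fisher's test. Analysis of secondary endpoints then names a chi-squared or Fisher test for superficial infection, all post-operative infections, microbial flora, adequacy of antibiotic treatment and rehospitalization. None of these is stratified.
- **Deferred detail.** Statistical methods announces a detailed analysis plan and allows changes to it until the database is unblinded.

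**The concern.** Blocked randomization within centers balances the arms inside each center. A center with a high infection rate then adds about equally to both arms, and its level largely cancels out of the difference. An ordinary two-sample standard error does not use this. It treats all patients in an arm as sharing one rate, so differences between centers stay in the variance. The interval then describes more sampling variation than the design produces.

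What is at stake is precision. One confidence limit decides the trial, and power is only 80%. For the binary secondary endpoints the same loss applies, and a continuity correction would add to it. Those endpoints are where harm from withholding antibiotics, such as superficial infection, would show.

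**Working it through.** **Inputs from the Sample size section:** "we assume that the incidence of organ/space SSIs in the reference group is 12" percent (the same rate is taken in the experimental arm); "With a non-inferiority margin of 5" percent; "a two-sided alpha risk of 5" percent; "a beta risk of 20" percent; 10% loss to follow-up; 738 per group, raised to 747 for the interim analyses.

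**Assumed, because the documents do not give it:** the between-center standard deviation (SD) of the infection rate. The number of centers and the block size in the simulation are also assumptions.

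**1. Reproduce the plan's figure.** Unstratified formula with unpooled variance:

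n = (1.960 + 0.8416)² × 2 × 0.12 × 0.88 / 0.05² = 663.1, so 664 per arm. Then 664 / 0.90 = 737.8, so 738 per group and 1476 in total.

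This matches exactly, so the planned size relies on no center adjustment.

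**2. Unstratified interval at the final size.** Evaluable per arm: 747 × 0.9 = 672.3. SE = √(2 × 0.12 × 0.88 / 672.3) = 0.01772. Half-width = 1.96 × SE = 3.47 points. This uses 1.96 and ignores any adjustment for the interim analyses.

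**3. Effect of stratifying.** With the same rate in both arms of a center, the variance ratio is R = 1 − SD² / (0.12 × 0.88). Stratified power, starting from the planned 80%, is Φ(2.8016/√R − 1.96).

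| Assumed SD | R | Half-width | Stratified power |
|---|---|---|---|
| 0 points | 1.000 | 3.47 | 80.0% |
| 3 points | 0.991 | 3.46 | 80.3% |
| 4 points | 0.985 | 3.45 | 80.6% |
| 5 points | 0.976 | 3.43 | 80.9% |
| 6 points | 0.966 | 3.41 | 81.3% |

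Some of that power gain comes from the design and not from the analysis. With stratified randomization, the unstratified rule has power Φ(0.8416/√R). At 6 points this is 80.4%, so the analysis itself adds about 0.9 of the 1.3 points.

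**4. Simulation check.** 20,000 runs per scenario, with blocks of 4, 20 or 40 centers, and center rates varying on the logit scale with SD 0 to 0.75. A logit SD of 0.5 corresponds to about 5 points and 0.75 to about 8 points.

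- One-sided error at a true difference of 5 points was 0.022 to 0.026 for the unstratified rule and 0.023 to 0.026 for Mantel-Haenszel.
- At logit SD 0.5 the mean half-widths were about 3.47 and 3.42 points. At 0.75 they were about 3.46 and 3.36.
- With 40 centers and no heterogeneity they were 3.470 and 3.472, so stratifying gained nothing.

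**5. Continuity correction.** Exact size of a nominal 5% chi-squared test at 672 per arm, without and with Yates' correction: 5.0% and 4.1% at a 12% event rate; 5.0% and 3.3% at an assumed 3%; 4.5% and 2.3% at an assumed 1%. The correction costs most for rare events.

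**The case against.** The strongest reply is that the primary rule is silent on center and does not rule it out. No interval method is named, a Mantel-Haenszel difference would satisfy the sentence as written, and the choice is one that an analysis plan normally makes. This stands. A reader might infer that the protocol prescribes a crude interval, but the text does not go that far. It is different for the binary secondary endpoints, where unstratified tests are named and the analysis plan would have to depart from them.

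Three stronger readings are tempting and are not supported:

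- **That the interval is invalid or the trial's error rate is at risk.** The simulated error stays near 2.5%, and any departure caused by ignoring center is on the conservative side.
- **That the protocol's own literature shows the centers will differ.** The range of 4 to 19% in Choice of evaluation criteria is between published studies. Those detailed there date from 1996 to 2016, and their antibiotic regimens differ or are unreported. It says nothing about centers of one network under one protocol.
- **That stratifying always helps and costs nothing.** With equal center rates there is no gain, and a center with patients in only one arm contributes nothing unless pooled.

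On Yates, the correction stands only in the general rule. The secondary-endpoint section names chi-squared without it, and it does not touch the primary interval. So it may not be meant for those endpoints, but the text leaves this open.

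**Conclusion.** The point holds as a minor one about efficiency. The design is stratified by center; the primary difference is worded without a center term, and the binary secondary tests are named without stratification. If the analysis follows that wording, it remains valid and is slightly conservative to the extent that centers differ.

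For an assumed between-center SD of 0 to 6 points around 12%, the variance falls by 0 to about 3.4%, the half-width by at most about 0.06 points against a 5-point margin, and power rises by 0 to about 1.3 points over the planned 80%. These figures rest on the assumed SD, equal rates in the two arms of a center, and no interim adjustment of the critical value. The planned sample size is unaffected.

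**What to change.** Before unblinding, state in the analysis plan:

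1. The primary decision uses the Mantel-Haenszel center-stratified risk difference with a variance suited to sparse strata (for example Sato's), and small centers are pooled by a rule fixed in advance.
2. The crude difference with its 95% interval is reported as a sensitivity analysis.
3. Binary secondary endpoints are compared with the Cochran-Mantel-Haenszel test, stratified by center, without continuity correction.

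The cost is a few sentences and a few lines of SAS code. The downside is that a pooling rule has to be chosen and defended, and that there is no gain, or a negligible loss, if centers turn out alike. No change to sample size or conduct is needed.

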##### Analysis of secondary endpoints

The patient-related endpoint, consisting of quality of life prior to surgery, on discharge, and on POD 30 after surgery, will be assessed in a mixed model analysis of variance with a Bonferonni-Holm closed testing procedure for post hoc analyses.

In terms of the infection-related endpoints, the proportion of patients with superficial SSIs will be assessed using a chi-squared test or Fisher’s test. The post-operative infection rates by POD 30, including SSIs and remote infections, will also be assessed using a chi-squared test or Fisher’s test. The number of antibiotic-free days between randomization and POD 30 will be assessed using Student’s *t*-test or a Wilcoxon test. The microbial flora will be assessed using a chi-squared test or Fisher’s test. The proportion of patients with adequate antibiotic treatment will also be assessed using a chi-squared test or Fisher’s test.

In terms of the surgery-related endpoints, morbidity and mortality (according to the Dindo-Clavien classification) will be assessed using a Wilcoxon test, LOS will be assessed using a chi-squared test or Fisher’s test, and the rehospitalization rate will be assessed using a chi-squared test or Fisher’s test.

Statistical analysis will be performed using SAS® software (version 9.4, SAS Institute Inc., Cary, NC, USA).

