#### Secondary outcomes

The secondary outcomes include three types: patient related, infection related, and surgery related.

The patient-related outcomes will include their quality of life prior to surgery, on discharge, and on POD 30, using the EuroQol 5D and SF36 questionnaires.

The principal infection-related outcome will be the proportion of patients with superficial SSIs, defined as infections that occur within 30 days of the intervention and affect the skin and subcutaneous tissues and for which at least one of the following signs is observed: pus coming from the superficial part of the incision, bacteria isolated from a liquid or tissue sample collected aseptically from the superficial part of the incision, a sign of infection (pain, tenderness, redness, burning, etc.) associated with deliberate opening of the superficial part of the incision by the surgeon (except if the culture is negative). Infection of the superficial part of the incision is diagnosed by the surgeon (or the physician attending to the patient). The definitions are based on that published by the CDC. Additional infection-related outcomes include the post-operative infection rates by POD 30, including SSIs and distant infections, the number of antibiotic-free days between randomization and POD 30, a description of the microbial flora, as found in the antibiogram of the perioperative sample that is collected in all cases, and the balance between antibiotic therapy and microbial resistance. The antibiotic treatment will be considered adequate if no bacteria are found in the perioperative sample or if all of the detected bacteria are sensitive to the administered antibiotic therapy. The antibiotic treatment will be considered inadequate if the perioperative sample is positive for resistant bacteria.

Surgery-related outcomes will include morbidity and mortality according to the Dindo-Clavien classification [25] and the CCI [26]; length of stay (LOS), defined as the number of days of hospitalization between surgery and discharge; and rehospitalization rate, defined as rehospitalization during the study period.

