#### Inclusion visit

The inclusion visit (which is the same as the screening visit) will include a physical examination, including cardiac blood flow, body temperature, and pain evaluation; a laboratory test battery (blood ion profile, ASAT, ALAT, total bilirubin, indirect bilirubin, alkaline phosphatase, GGT, amylase, lipase, CRP, hCG (if applicable), procalcitonin levels, and leukocyte count).

The laparoscopic appendectomy will then be performed, regardless of the hour or day, and the randomization performed after the appendectomy.

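### Pre-surgery quality of life, measured before randomization, is listed as one of three outcome times, with no stated baseline adjustment or common baseline mean

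*Protocol article*

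**What the plan says.** The Secondary outcomes section defines the patient-related outcome as "quality of life prior to surgery, on discharge, and on POD 30, using the EuroQol 5D and SF36 questionnaires". The Analysis of secondary endpoints section repeats the three times: the endpoint, "consisting of quality of life prior to surgery, on discharge, and on POD 30 after surgery, will be assessed in a mixed model" ANOVA, is followed by a "Bonferonni-Holm closed testing procedure for post hoc analyses".

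The Inclusion visit section has "the randomization performed after the appendectomy", and the Randomization section likewise places allocation at the end of surgery. The first of the three measurements therefore precedes allocation and any study product.

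Neither section on quality of life calls the pre-surgery score a baseline or a covariate, or says that its mean is taken to be the same in both arms. Neither names the treatment contrast (group main effect, group-by-time interaction or difference at a given visit), and the post hoc comparisons are not listed. The Statistical methods section adds: "A detailed statistical analysis plan will be defined and validated by the study’s scientific advisory board".

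**The concern.** A score taken before randomization can differ between arms only by chance. Its use in a treatment comparison is to explain variation between patients in the later scores. Listed simply as one more outcome time, it does not do that job unless the model is told to use it.

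What is at stake is precision. The trial collects the pre-surgery EuroQol 5D and SF36 from every patient. If the treatment comparison then ignores those scores, or uses them only by subtraction, part of their information is lost. Quality of life is the only patient-related outcome named, and a less precise comparison is more likely to miss a real difference between arms.

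**Working it through.** **The plan's own figure.** The article gives no SD, effect size, correlation or power for quality of life, so there is nothing to reproduce for this endpoint. The primary sample size was checked to confirm that it is a separate matter. With 12% in both arms, a 5% margin, two-sided 5% alpha and 80% power:

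- n per group = (1.9600 + 0.8416)² × 2 × 0.12 × 0.88 / 0.05² = 663.1, rounded up to 664.
- 664 / 0.9 = 737.8, rounded up to 738 per group, or 1476 in total.

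This matches the stated figure before the increase for interim analyses. Nothing below changes it.

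**Assumptions for quality of life (not from the article).** Equal SD at each time, set to 1; compound symmetry with correlation ρ = 0.3, 0.5 or 0.7; complete data; no effect at the pre-surgery time.

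**POD 30 comparison.** The variance of the between-arm difference is (2/n) × v, where

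- unadjusted: v = 1
- change from baseline: v = 2(1 − ρ)
- baseline-adjusted: v = 1 − ρ²

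Efficiency relative to the adjusted analysis is 1 − ρ² for the unadjusted comparison and (1 − ρ²) / [2(1 − ρ)] = (1 + ρ)/2 for change. If the adjusted analysis has 80% power at two-sided 5%, the power of another contrast is Φ(√efficiency × 2.8016 − 1.9600).

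| ρ | Unadjusted: efficiency | power | Change: efficiency | power |
|---|---|---|---|---|
| 0.3 | 0.91 | 76% | 0.65 | 62% |
| 0.5 | 0.75 | 68% | 0.75 | 68% |
| 0.7 | 0.51 | 52% | 0.85 | 73% |

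For example, at ρ = 0.5: √0.75 × 2.8016 − 1.9600 = 0.466, and Φ(0.466) = 0.68.

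**Mean of the two post-operative times, same effect at both.** The adjusted v is (1 + ρ)/2 − ρ² = 0.56 / 0.50 / 0.36. The change contrast has v = 1.5(1 − ρ) = 1.05 / 0.75 / 0.45, so its efficiency is 0.53 / 0.67 / 0.80.

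**Does the mixed model recover the loss by itself?** With the pre-surgery score as a response and each arm given its own mean at each time, the generalized least squares variance of the POD 30 difference is 2.00 (in units of 1/n) at every ρ, the same as the unadjusted comparison. If the pre-surgery mean is constrained to be common to both arms, the variance becomes 1.82 / 1.50 / 1.02. That equals 2(1 − ρ²), the covariate-adjusted value. Keeping the score in the response is therefore harmless with the constraint and inefficient without it.

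**The case against.** The strongest reply is that the sentence in the article is compatible with a fully efficient model. A mixed model that keeps the pre-surgery score as a response with a common baseline mean loses nothing, so listing three times is not in itself an error. This stands, and the fix accepts that model as an alternative.

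A second reply is that covariates, contrasts and the Holm family for a secondary endpoint usually belong in the SAP, which is not shown. This stands in part, and is one reason why the point is minor. However, the article already fixes the model family, the three response times and the multiplicity method. An SAP that followed that text literally could carry the inefficiency forward.

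A third reply is that the loss may be small. The pre-surgery score is taken during acute illness, and its correlation with POD 30 could be low. The unadjusted loss is ρ², only 9% at 0.3, and it vanishes as ρ falls to 0. This is fair for the unadjusted comparison. The change contrast behaves the opposite way: its efficiency, (1 + ρ)/2, falls towards one half. All of these contrasts remain unbiased under randomization; only precision is at issue.

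Two stronger readings are tempting. A reader might infer that the treatment effect is diluted to two thirds, since averaging effects of 0, d and d gives 2d/3. That follows only if the test is the group main effect over all three times. A group-by-time or per-visit contrast is not diluted. A reader might also infer that a Holm step is spent on a comparison that is null by design. That follows only if the arms are compared at the pre-surgery time. The article specifies neither test.

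**Conclusion.** The point holds as a minor one. A pre-randomization score is listed as an outcome time, with no stated baseline adjustment or common baseline mean, and the usual unconstrained contrasts then lose precision. Against 80% power for the adjusted POD 30 comparison, the unadjusted comparison has about 76 / 68 / 52% and the change contrast about 62 / 68 / 73% at correlations of 0.3 / 0.5 / 0.7.

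These figures rest on assumed correlations, equal SDs, compound symmetry and complete data. The facts about the listed times and the timing of randomization come directly from the article. Dilution of the effect and a wasted Holm step are possibilities under particular tests, not established features of the plan.

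**What to change.** State in the protocol or the SAP that the treatment effect on EQ-5D and SF-36 is the between-arm difference at discharge and at POD 30, estimated from the mixed model. The pre-surgery score enters either as a covariate or as a response with baseline means constrained equal between arms. Holm adjustment covers those two contrasts only. Report the pre-surgery score as a baseline characteristic and remove it from the list of outcomes.

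The cost is about one sentence, with no new data and no additional patients. It should be settled before unblinding and validated by the scientific advisory board, as the Statistical methods section requires for any modification.
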